### Sample size and power calculations

The RCT was designed to enroll an average of 6 patients for each of 56 participating clinicians. The sample size was calculated on the basis of our primary hypothesis, that the intervention group (motivation feedback) would be more effective than the control group (treatment as usual) in enhancing treatment engagement, as measured with the Service Engagement Scale (primary outcome) at 12 months after baseline assessment. The difference between the motivation feedback group and control group for the primary outcome is based on a power of 0.80 and an alpha of 0.05 (two-tailed). Earlier studies regarding differences between feedback and treatment as usual (control) conditions have shown effect sizes (standardized mean differences) ranging from 0.34 to 0.92 [16,17], but were based on treatment progress and not (solely) on treatment motivation. One RCT studying the effects of treatment adherence therapy in patients with psychotic disorders used the SES as outcome measure and found an effect size of 0.39 [80]. Therefore, we expect an effect size of approximately 0.40. Using an unpaired t-test statistic, this resulted in a minimum of 123 subjects per condition. However, as patients are clustered within clinicians, and clinicians are clustered in teams, the patient and clinician observations can not be considered as independent of each other. The sample size was therefore adjusted by the (variance inflation) factor f = 1 + (m – 1)ρ, to account for the variance that would have been achieved had there been no clustering. The cluster size (m) is 6 (patients per clinician) and the within-cluster correlation (ρ) was estimated from a previous study to be around 0.07 [21]. Thus, the computed sample size was inflated by 1.35 to be at least 166 subjects per condition (minimally 332 in total). The SES is rated by clinicians and so we expect minimal loss to follow-up on the primary outcome, but to be on the safe side we will aim for 350 patients as the total sample size.

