### Statistical analyses

The data of the RCT will be analyzed according to the intention-to-treat principle. Baseline comparability between the intervention group and control group in demographic and clinical variables will be evaluated with independent samples t-tests and chi-square tests. Furthermore, non-responders (i.e. eligible patients who chose not to participate in the study) will be compared to responders with respect to background demographic and clinical variables with independent samples t-tests and chi-square tests. Logistic regression analysis will be applied to test for differences between the motivation feedback and control group with respect to the primary and secondary outcomes that are dichotomous variables, while (multiple) linear regression analysis will be used in case of continuous outcome variables. For individual categorical outcome variables, the effectiveness will be determined by odds ratios, including p-values (two-tailed). The effectiveness of the variables combined will be determined by ROC-curves (for categorical outcomes) and the individual odds ratios, R2 and the individual regression coefficients (for continuous outcomes). The Hosmer and Lemeshow goodness-of-fit test will be used in case of logistic regression. In case of multiple regression analysis the classical regression diagnostics will be applied for normality, (non)linearity, heteroscedasticity, (influential) outliers and interaction. A subgroup analysis will be performed for patients with psychotic disorders for the effects of the intervention upon their antipsychotic medication adherence. The analyses will be performed both unadjusted and adjusted for baseline differences of the distributions between the two treatment groups. In analyzing a specific outcome variable, the baseline score of that variable will be used as covariate. The analysis will be extended using multilevel analyses that takes the nesting of measurements into account. A clustering of outcomes is likely since a single clinician may treat several patients, and clinicians are clustered into teams. Multilevel modelling will be performed to check for any clustering effects on the primary outcome. In the multilevel analyses we consider the two measurements as the first level and the patient as the second level. We will explore whether the different treatment locations (FACT teams) and institutions (MHC Breburg and MHC WNB) can be considered as random factors in the modeling. We will identify predictive factors in estimating the outcome and whether there are predictive factors dependent on the type of treatment condition (interaction between baseline variables and treatment effect). Furthermore, we will take into account to what extent patients were exposed to the intervention by analyzing the dose-effect relationship. We expect (as is the case in most empirical studies in a psychiatric setting) that missing data will occur. We expect that the data will be Missing At Random (MAR), which is allowed to be a function of the observed variables (both covariates and outcome variables). If the assumption of MAR is violated, the pattern mixture model approach will be applied. In case predictor variables are missing, the method of multiple imputations or the maximum likelihood estimation method will be applied.

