### Ethical considerations

The current research protocol was endorsed by the Medical Ethical Committee for Mental Health Care Institutions (METiGG) and by the committees for scientific research within the two mental health institutions where the data will be collected (MHC WNB and MHC Breburg). The collected data are treated according to the Medical Confidentiality Rules, and are kept in locked files cabinets. Every patient will be assigned a patient number, so that processing of the data will occur anonymously. Access to data is limited to members of the research group and the medical ethical committee (METiGG). The study will be conducted in accordance with the Helsinki Declaration. As mentioned previously, written informed consent will be obtained for all clinicians and patients that are entered into the study. Patients and clinicians are free to refuse participation at any time during the research period, without having to disclose any reason why.

Patients that are included in the study will receive an incentive of € 15, - after every completion of an extensive measurement (baseline and follow-up). Thus, if a patient has completed both measurement occasions, he or she will have received € 30, - in appreciation of his/her cooperation. These incentives are introduced in order to increase the response rate, since it is expected that in this patient population with severe mental illness and possibly with motivational problems, the response rate would otherwise turn out too low. The effects of the intervention are unknown at this moment, and therefore we think it is justified to allocate patients randomly over the two conditions.

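### The stated analyses of 12-month TEQ, MANSA and HoNOS need a narrower missing-at-random condition than the plan allows, and leave unused the 12-month engagement data that do not depend on the patient taking part

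*Protocol article*

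**What the plan says.** All of the following is in the protocol article.

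- **Outcome models (Statistical analyses).** Continuous outcomes are analysed by linear regression. "In analyzing a specific outcome variable, the baseline score of that variable will be used as covariate". A second version widens the adjustment: "The analyses will be performed both unadjusted and adjusted for baseline differences of the distributions between the two treatment groups". The multilevel extension adds no further outcome: "In the multilevel analyses we consider the two measurements as the first level and the patient as the second level".
- **Missing data (same section).** The authors expect data to be MAR, "which is allowed to be a function of the observed variables (both covariates and outcome variables"). The fallback is conditional: "If the assumption of MAR is violated, the pattern mixture model approach will be applied". The one sentence that names imputation or likelihood estimation is about predictors: "In case predictor variables are missing, the method of multiple imputations or the maximum likelihood estimation method will be applied".
- **Where 12-month engagement comes from.** Under Sample size and power calculations: "The SES is rated by clinicians and so we expect minimal loss to follow-up on the primary outcome". Under Treatment engagement, missed appointments and reasons for drop-out are taken from patient files.
- **What needs the patient.** TEQ and MANSA are patient questionnaires. HoNOS is scored from an interview with the patient by the case-manager and a research assistant.
- **Expected non-response.** Ethical considerations justifies the payment per assessment by the concern that, in patients with severe mental illness and "possibly with motivational problems, the response rate would otherwise turn out too low".

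**The concern.** MAR supports an analysis only when the observed variables that drive missingness are in the analysis model or in an imputation model. The plan's MAR statement is broad enough to cover dependence on 12-month engagement. Its models for TEQ, MANSA and HoNOS contain nothing measured at 12 months except the outcome itself.

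In this trial the omission matters more than usual. The primary outcome is engagement, and engagement is a plausible driver of whether a patient completes the 12-month assessment. If less engaged patients are the ones lost, the secondary comparisons describe mainly engaged patients. If completion is tied to engagement more closely in one arm, the arm contrast is biased as well. One conceivable route is that only feedback patients are asked for monthly questionnaires. The trial would hold a marker of the selection and not use it.

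**Working it through.** The plan gives no missing-data figure to reproduce, so the check has two parts.

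**1. Text comparison**

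| Question | What the plan provides |
|---|---|
| What may missingness depend on? | Observed covariates and outcome variables |
| What do the outcome models condition on? | Arm, own baseline; in one version other baseline differences; in the multilevel version the same two occasions |
| For what is imputation or likelihood estimation named? | Missing predictors |
| When does the pattern-mixture model apply? | If MAR is violated |
| Does any step bring 12-month SES or file data into a missing TEQ, MANSA or HoNOS? | None stated |

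Suppose missingness depends on 12-month SES and SES is observed. MAR in the plan's broad sense then holds, so the fallback is not triggered. The single-outcome models are nevertheless not protected, because SES is not in them.

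**2. Size, by large-sample simulation**

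Input from the plan: SES effect 0.40 SD.

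Assumptions, none of them in the plan:
- baseline-to-follow-up correlation 0.5;
- correlation of 12-month SES with the secondary outcome 0.3 to 0.5;
- no true effect on the secondary outcome;
- about 70-75% completing;
- completion logistic in 12-month SES, coded so that higher means more engaged.

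The arm coefficient among completers, adjusted for own baseline, is compared with the coefficient after imputation that uses 12-month SES.

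| Link between completion and SES | Bias, completers | Bias, imputation with 12-month SES |
|---|---|---|
| Same in both arms | -0.01 to -0.03 SD | about 0.005 SD or less |
| Logit slope 0.5 control, 1.5 feedback | +0.03 to +0.05 SD | about 0.005 SD or less |
| Logit slope 1.5 control, 0.5 feedback | -0.05 to -0.09 SD | about 0.005 SD or less |

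A separate run with 26-33% missing gave zero bias when SES and the outcome had no residual correlation. When the link was present in the control arm and absent in the feedback arm, the bias was about -0.06 SD (residual correlation 0.3) to about -0.11 SD (0.5). Adding baseline SES as a covariate did not remove it.

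**Consequence for the test**

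- Completers: 255 of 350, or 73%.
- Design effect from the plan: 1 + (6 - 1) × 0.07 = 1.35.
- Residual variance: 1 - 0.5² = 0.75.
- SE = √(4/255 × 0.75 × 1.35) = 0.126 SD.
- False-positive rate at absolute bias b: Φ(-1.96 + b/SE) + Φ(-1.96 - b/SE).

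| Absolute bias (SD) | b/SE | False-positive rate |
|---|---|---|
| 0.01 | 0.08 | 5.1% |
| 0.03 | 0.24 | 5.7% |
| 0.05 | 0.40 | 6.8% |
| 0.09 | 0.71 | 11.0% |

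**The case against.** The strongest objection is that this is detail for a full analysis plan. The article states an MAR assumption, names a fallback, fixes baseline adjustment and adds a multilevel model. Auxiliary variables are usually chosen elsewhere. That carries weight against calling it a serious defect. It does not dispose of the point, because the article addresses missing data directly and ties its named method to predictors, while the outcomes most exposed to loss get nothing that uses the engagement data.

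Several stronger readings are tempting, and the text does not support them.

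- **That the plan contradicts its own MAR assumption, or that the assumption requires 12-month engagement.** The wording is permissive. The outcome variables could mean the earlier value of the same outcome, which a two-occasion likelihood model does use.
- **That imputation is ruled out for outcomes.** The sentence names predictors but does not exclude outcomes.
- **That own baseline is the sole basis.** There is also the version adjusted for baseline differences, and the pattern-mixture fallback. Neither brings in 12-month engagement.
- **That engagement data exist for every patient not assessed.** For patients who leave treatment early, Procedures and randomization names only the reason for ending and total treatment duration. Minimal SES loss is an expectation.
- **That the plan predicts heavy motivation-related loss.** The remark on response explains an incentive meant to prevent it. The case-manager's presence is also meant to raise response. No rate is given.

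The size is also hypothetical. Material bias needs a link between engagement and completion that differs by arm, and the monthly questionnaires make this conceivable but do not show it.

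**Conclusion.** The point holds as a modest improvement. As written, the analyses of 12-month TEQ, MANSA and HoNOS are valid under a narrower MAR condition than the plan allows, and they set aside engagement data that the trial intends to collect anyway.

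If completion depends on engagement alike in both arms, the effect on the arm contrast is negligible. If the dependence differs by arm, the bias is roughly 0.03 to 0.09 SD in either direction, and at the top of that range the nominal 5% test runs at about 11%. An extreme case, with no link at all in the feedback arm, goes slightly beyond that range. All of these figures rest on the assumed completion, correlations and slopes. The primary SES comparison is little affected, and missed appointments, taken from files, do not depend on the patient's assessment.

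**What to change.** State how missing 12-month TEQ, MANSA and HoNOS are handled: multiple imputation carried out separately within each arm, or a joint likelihood for the outcomes. Use as auxiliaries the 12-month SES where available, percentage of missed appointments, drop-out status and the baseline values of all outcomes. Keep the own-baseline regression on completers as a sensitivity analysis, and leave the pattern-mixture model for departures from MAR.

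The cost is a few sentences and modest extra programming, with no new data collection. The downside is reliance on an imputation model that includes an unblinded clinician rating, which may itself be missing for some patients who left care. Imputing within arm eases the first problem; the file data partly cover the second.

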## Methods/design

### Aims

The study has three main objectives. The primary objective is to determine the effects of the motivation feedback intervention on treatment engagement (TE) of patients with psychotic and/or personality disorders. Secondary outcomes are the patient’s treatment motivation, psychosocial functioning and quality of life. To this end, clinicians will be randomly assigned to either of two groups; one group will generate SDT-based feedback on the motivation of their patients while the other group will not.

The second objective is to determine the factors associated with the effect of our motivation feedback intervention upon the primary and secondary outcomes. Several demographic and clinical factors as well as factors that have a theory-based and/or empirically established relationship with the outcomes will therefore be assessed. At the moment, it is unclear which exact factors are most important so this will be studied explorative.

The third and final objective of the study is to determine which theory of motivation is most plausible for the dynamics of TE and treatment motivation in patients with psychotic disorders and personality disorders in outpatient treatment. The models selected here are the Transtheoretical Model (TTM) [28], the Integral model of treatment motivation (IM) [12] and Self-Determination Theory (SDT) [27]. In a literature review that we have performed earlier, we have described these theories in detail, including their differences and similarities [29]. We will explore which of three theories (i.e. TTM, SDT, and IM) is most supported by the data in predicting treatment motivation and engagement. It is possible that different subcomponents of these theories will be integrated in a novel theoretical-empirical model tailored to this specific population.

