
For monthly measurements (i.e. the motivation feedback graph for patient and therapist, and the therapist motivation) the method of mixed modelling will be applied. This highly flexible method enables two level models: repeated measurements (level 1) and patient level (level 2).

The three motivational theories will be modelled with Structural Equation Modelling (SEM), in order to study their fit to the empirical data, their predictive power and parsimony (i.e. whether the model can be simplified without substantially reducing the model fit and predictive power). The three motivational theories will be studied exploratively to determine which theoretical constructs are most plausible (i.e. clinically relevant and statistically significant) for the prediction of the outcome variables. The difference of the two -2log-likelihood tests (including the difference of degrees of freedom) will be used for testing differences between nested models, and information criteria will be used for differences between non-nested models (i.e. Akaike Information Criterion/AIC, Bayesian Information Criterion/BIC and adapted BIC). Where relevant, the 95% confidence intervals and/or P-values (two-tailed) will be reported.

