Regarding the theory comparisons it should be noted that SDT will be tested most rigorously in this study, since this theory will be used as the basis for the intervention in this study and its core theoretical components will be manipulated (i.e. the basic psychological needs will be supported by clinicians, and motivational types will be known and responded to by clinicians). Although the other two theories are not tested so rigorously (i.e. they are not part of the intervention), the core theoretical constructs of IM and TTM are followed prospectively over the course of 12 months in order to determine if the constructs behave as the theories suggest and to see if they are able to predict treatment motivation and treatment engagement at follow-up. The design of our study fulfils most of the criteria that have been suggested by Noar and Zimmerman [81] for theory comparison studies. The criteria are: 1) having a longitudinal design, 2) using Structural Equation Modelling, 3) including past behaviour and (4) demographics in the model tests, 5) including non-college participants in the sample, 6) having a strong sample size (N>200), 7) utilizing multiple samples in model testing, 8) utilizing samples from more than one country, 9) having more than one dependent variable (e.g. motivation and behaviour), 10) examining more than one behaviour, 11) comparing more than two theories and (12) empirically examining an integrated model [81]. All criteria except 8 and 10 are fulfilled by our design. Furthermore, most previous studies employing the TransTheoretical Model have only measured the stages of change, while the model also incorporates other constructs. The current study measures both the stages of change, the processes of change, self-efficacy and the decisional balance constructs. Thus, a strong aspect of this study is that it includes all core theoretical constructs of the three motivational theories.

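### Theory comparison: constructs are selected partly by significance and the models judged on the same cohort, so predictive power will look too good; the claim that multiple samples are used is unsupported

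*Protocol article*

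**What the plan says.** All places are in the protocol article.

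- **Statistical analyses.** The three theories are modelled by SEM "in order to study their fit to the empirical data, their predictive power and parsimony". The aim is to "determine which theoretical constructs are most plausible (i.e. clinically relevant and statistically significant) for the prediction of the outcome variables". Nested models are compared by the difference in −2 log-likelihood, non-nested models by AIC, BIC and adapted BIC. The work is labelled exploratory: "The three motivational theories will be studied exploratively".
- **Aims.** The theory comparison is one of three main objectives. "It is possible that different subcomponents of these theories will be integrated in a novel theoretical-empirical model tailored to this specific population".
- **Strengths.** Twelve published criteria for theory-comparison studies are listed. Criterion 7 is "utilizing multiple samples in model testing" and criterion 12 is "empirically examining an integrated model". The article concludes: "All criteria except 8 and 10 are fulfilled by our design". It therefore claims both 7 and 12.
- **Sample size and power calculations.** There is one trial cohort, with a target of 350 patients.
- **Possible further samples.** The two institutions appear only as candidate random factors (Statistical analyses). Diagnosis appears only as a covariate (Procedures and randomization). The one subgroup analysis, in psychotic disorders, concerns medication adherence.

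**The concern.** Selecting constructs, estimating their coefficients and judging the result all draw on the same patients. A construct kept because it reached significance tends to have an overestimated coefficient in the data that selected it. AIC and BIC charge for the parameters in the final model but not for the search that chose them. R² and information criteria computed on those data therefore flatter any model assembled in this way, whether it is a pruned single theory or a merged one.

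The Discussion asks which theory best predicts the outcomes and presents the identified mechanisms as a basis for future interventions. If predictive power is overstated, the third objective could recommend a model whose performance does not recur in new patients. A reader who relies on the Strengths section would believe that testing in several samples guards against this.

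**Working it through.** **1. The passages side by side.** The selection rule and the yardsticks stand in Statistical analyses. The article names no split, second cohort, multi-group model or cross-validation for the theory models. The criterion 7 claim in Strengths thus has no stated design element behind it. Two institutions and two diagnostic groups exist and could serve as samples, but the article does not say that the models are tested in each.

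**2. Constructs that can be counted in the article.**
- SDT: 4 (external, introjected and identified motivation; autonomy support).
- IM: 7 (motivation to engage plus six determinants).
- TTM: 13 at most (stage; 20 statements / 2 = 10 processes; self-efficacy; decisional balance).

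**3. Chance of importing at least one irrelevant construct.** If one theory is true, *k* foreign constructs have no effect, and each independent test is at 0.05, the chance is 1 − 0.95^k:
- SDT true, k = 7 + 13 = 20: 0.64
- IM true, k = 4 + 13 = 17: 0.58
- TTM true, k = 4 + 7 = 11: 0.43

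**4. Simulation.** The article gives no figure to reproduce, so this step is illustrative. Linear regression stands in for SEM, with N = 350, independent constructs and patients, and a true R² of 0.10 spread equally over the true theory's constructs. Constructs with p<0.05 in their own theory's model are kept. The pruned true theory is what remains of the true theory; the merged model is the union of everything kept. There were 1,500 runs per row.

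| True theory | AIC prefers merged over pruned true theory | BIC does | Merged: apparent → new R² | Pruned true theory: apparent → new R² | Full true theory: apparent → new R² |
|---|---|---|---|---|---|
| SDT | 61% | 19% | 0.119 → 0.064 | 0.106 → 0.077 | 0.109 → 0.087 |
| IM | 55% | 17% | 0.116 → 0.041 | 0.105 → 0.052 | 0.118 → 0.079 |
| TTM | 42% | 12% | 0.107 → 0.012 | 0.100 → 0.019 | 0.133 → 0.063 |

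The percentages move by a few points between repeat runs.

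**5. Where the loss arises.** In new patients, importing foreign constructs costs 0.077 − 0.064 = 0.013, 0.052 − 0.041 = 0.011 and 0.019 − 0.012 = 0.007. Pruning the true theory by significance costs 0.087 − 0.077 = 0.010, 0.079 − 0.052 = 0.027 and 0.063 − 0.019 = 0.044. Pruning dominates for IM and TTM; for SDT the two are about equal. Even the full theory shows some optimism, because it too is fitted and scored on the same patients.

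**6. Fewer constructs.** TTM instruments places self-efficacy and decisional balance inside the IM questionnaire, and Table 1 appears to schedule the processes scale at one occasion only. TTM may then contribute one stage variable or four stage subscales. With one, k falls to 8 (SDT true, 0.34) or 5 (IM true, 0.23). AIC prefers the merged model over the pruned true theory in about 21–44% of runs and BIC in 13% or fewer. The merged model's R² in new patients is then about 0.05–0.09.

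**7. Effect of validation.** A related simulation took SDT as true, added significant rivals to the full theory, used 9, 16 or 21 rivals with no effect, and set true R² at 0.10–0.30 and construct correlation at 0 or 0.3. Same-patient AIC preferred the merged model in 33–67% of runs and BIC in 10–24%. With selection repeated inside 10-fold cross-validation it won in 8–12%; with selection and fitting in one half and scoring in the other, in 2–8%.

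**The case against.** - **The work is exploratory and integration is conditional.** Both are true: Aims says only that merging is possible. But Strengths counts the integrated-model criterion as fulfilled, and optimism arises from significance selection within a single theory too.
- **Selection also requires clinical relevance.** This stands. The article gives no threshold for it, however, so its protection cannot be sized, and the simulation leaves it out.
- **Validation may be in a fuller plan.** It may, and its absence from an article is not in itself a fault. What can be faulted is what the article does state: a selection rule, yardsticks for judging the models, and a claim of multiple samples without naming any.
- **The merged model tends to beat even a true theory.** A reader might infer this from the 64% in step 3, but the documents do not support it as a general statement. Against the pruned true theory it is a minority result when TTM is true, with fewer constructs, and under BIC, one of the planned criteria. The comparator matters as well: against the full theory with all its constructs, the merged model wins by AIC in 65–88% of runs and by BIC in 52–100%, largely because it has fewer parameters.
- **Criterion 7 is falsely claimed.** This too might be inferred, but it goes beyond the text. Two institutions or two diagnostic groups could meet the criterion. The claim is unsupported, not shown to be false.

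**Conclusion.** The point holds in a limited form. Following the stated rule on one cohort gives optimistic predictive power, and nothing in the article corrects for it. With the largest construct counts, an apparent R² of about 0.11–0.12 for a merged model corresponds to 0.01–0.06 in new patients; for the pruned true theory, 0.10–0.11 corresponds to 0.02–0.08. Importing rival constructs is a small part of the drop, about 0.01. A merged model can outrank a true theory on the same data: roughly 20–65% of runs by AIC and 7–19% by BIC against the pruned true theory.

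These sizes rest on assumptions that are not in the documents: the 0.05 threshold, a true R² of 0.10 spread evenly, independent constructs and patients, and regression in place of SEM. The lowest values come from spreading that R² over 13 weak constructs. The direction of the bias does not depend on these choices; its size does. The third objective is affected. The comparison of motivation feedback with usual treatment is not.

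**What to change.** Keep the SEM and the information criteria, and add validation:

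1. Cross-validate by leaving out whole randomised units (teams or clinicians), with construct selection repeated inside every fold. Alternatively, build the models in one institution or diagnostic group and test them, coefficients unchanged, in the other.
2. Report validated beside apparent predictive power for each theory and for any integrated model. Prefer the integrated model only if its validated error is lower.
3. In Strengths, name the samples that meet criterion 7, or remove it from the criteria described as fulfilled.

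The cost is some extra analysis of data already being collected, and a reported predictive power that is smaller and more variable. Testing across institutions or diagnoses also leaves fewer patients for building the models. No change to recruitment, assessments or the primary analysis is needed.
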